|  |  |                                                                   | 
on the primary behaviour problems outcome at 3-months and the secondary behaviour problems outcome at 12-months.
 
 
To conduct an exploratory post-randomisation effect modifier analysis to see whether contact within clinical services outside of the service that the child had been referred to up to 3-months influences the effect of STEPS on the primary behaviour problems outcome at 3-months, and if such clinical contact up to 12-months influences the effect of STEPS on the behaviour problems secondary outcome effect at 12-months.
 
To conduct an exploratory analysis to see if STEPS reduces the likelihood of a clinical diagnosis being made and medication prescribed by the 12 months follow up.
 
                                                                                                                                                                                                                                                                                                                                                                                                                                                                                                                                                                                                                                                                                                           |

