## 4. Background & Rationale

Attention-deficit/hyperactivity disorder (ADHD) is a common neuro-developmental condition characterised by symptoms of inattention and/or impulsivity-hyperactivity (Dalrymple, Maxwell, Russell, & Duthie, 2019). It is associated with a range of academic, employment and social negative outcomes and impairment (Dalsgaard, Mortensen, Frydenberg, & Thomsen, 2013; Erskine et al., 2013; Fletcher, 2014; Moyá, Stringaris, Asherson, Sandberg, & Taylor, 2014; Polderman, Boomsma, Bartels, Verhulst, & Huizink, 2010). In 2012, annual ADHD-related health, social care and education costs in the UK were estimated at £670 million (Telford et al., 2013). These negative impacts are often driven by a broader pattern of behaviour problems (e.g., oppositional, disruptive, defiant and challenging behaviours) which are extremely common, in addition to the symptoms of inattention and hyperactivity/impulsivity themselves (Podolski & Nigg, 2001). Effective multi-modal treatments for ADHD exist but access to them in the UK is currently limited by budgetary constraints and there are long waiting lists for specialist expert assessment, diagnosis and treatment (The Children's Commissioner, 2016). In 2014, The House of Commons Health Committee reported that even maximum acceptable waiting times for complex cases of neuro-developmental disorders such as ADHD were already as long as 15 weeks in 2013 (Committee, 2014). In terms of actual waiting times, the Children's Commissioner Lightning Report in 2016 found up to 200 days delay to initial assessment (The Children's Commissioner, 2016). Prolonged waiting time may lead to families feeling unsupported during this stressful period and, importantly, to exacerbation of their difficulties, a decrease in motivation, poorer engagement and premature dropout with regard to future treatment (McGarry et al., 2008).

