### **10.3.5 Clinical diagnosis**

*Risk ratio at T5 as exploratory outcome.*

Information about ADHD diagnosis will be extracted from medical records at 12-month follow-up and recorded on the Assessment & Diagnosis form (Appendix 1). In case it is not possible to access a child's medical record, information will be collected directly from a parent (via a phone call). A presence of ADHD diagnosis will be coded as 1 and absence as 0. In addition, if other diagnosis has been given, information about the type of diagnosis will be recorded for descriptive purposes.

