## **13. Sample size**

A total of 352 parents and their children will be recruited into the study. This power calculation is based on projected effects at the primary endpoint (3 months post-randomisation). As behaviour problems measured with the ODD subscale of the SNAP-IV questionnaire (Swanson et al., 2001) is our primary outcome, we estimated the smallest difference of clinical importance between STEPS and WAU to be equivalent to an effect size  $d = 0.4$  standard deviations based on the NICE guidance supporting the use of PT for the treatment of ODD or conduct disorder (Lundahl, Risser, & Lovejoy, 2006). A within trial drop-out rate of 25% is assumed. This is higher than in most previous trials of face-to-face PT programmes because of the unsupported nature of STEPS in OPTIMA. We will monitor drop-out rates during the internal pilot and, if necessary, recalculate the sample size if it is higher than the 25% estimated. Using Stata (version 14.0) command *sampsi*, ANCOVA analysis with a conservative zero correlation assumed between baseline and primary endpoint SNAP-IV ODD score, a two-sided test and an alpha of 0.05, we estimated that 176 individuals will be needed per trial arm (total n = 352) to provide 90% power to test the hypothesis that STEPS is superior to WAU.

[figure not shown]

Figure 1. OPTIMA enrolment, group allocation and follow-up flowchart.

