The main analysis will follow the intention to treat (ITT) principle as much as possible (Sullivan et al., 2018; White et al., 2012). A mixed effects linear analysis of covariance (ANCOVA) model with repeated measures will be used with the SNAP-IV ODD scores at three (primary outcome), six, nine and 12 months (secondary outcomes) post-randomisation as the dependent variables, and intervention group, time point, intervention group by time point interaction, baseline SNAP-IV ODD score, and the trial centre stratification variable as independent variables, with the interaction term used to extract the primary and secondary outcome STEPS vs WAU mean differences and associated 95% confidence intervals at the four time points. Similar statistical models will be used to test for intervention effects on the other continuous secondary and exploratory outcome scale scores (average levels of directly observer-rated child behaviour problems (ESO), parent-rated hyperactivity/impulsivity and inattention, parenting style, satisfaction and efficacy, child-parent closeness and parenting-related strain) with the scores extracted at the timepoints listed in section 10 'Measures and outcomes'. For the binary exploratory diagnosis and medication outcomes we will use modified Poisson regression with robust standard errors to estimate STEPS vs WAU relative risks (and associated 95% confidence intervals) for getting a diagnosis and being prescribed medication (Zou, 2004).

In addition to ITT analysis, we will undertake a complier average causal effect (CACE) sensitivity analysis (Angrist, Imbens, & Rubin, 1996; Dunn et al., 2015) on the ODD outcome primary outcome at 3 months (T2) and ODD secondary outcome at 12 months (T5), to estimate treatment effects in those who completed at least two modules of the STEPS app (i.e., those that complied with the intervention).

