### **19.3 Health economic analysis**

#### **Is STEPS cost- effective compared to WAU over the 3-month and 12-month follow-up periods?**

The economic evaluation will adopt the NHS/personal social services perspective preferred by NICE, but will also include education-based services, given the age of the population. Resource-use data collected using the CA-SUS will be costed using nationally applicable unit costs (e.g., PSSRU Unit Costs of Health and Social Care, NHS Reference Costs, BNF for medications). The STEPS app will be costed in consultation with the system developers.

The primary economic evaluation will be a cost-utility analysis carried out at 3-months post-randomisation with outcomes expressed in terms of quality adjusted life years (QALYs), using the CHU9D proxy completed by a parent. Secondary economic analyses will include: (i) a cost-utility analysis at 12-months post-randomisation to assess cost-effectiveness subsequent to formal assessment and treatment; (ii) a cost-effectiveness analysis undertaken at both 3-months and 12-months using the primary clinical measure of outcome (SNAP-IV ODD score) and (iii) a cost-utility analysis undertaken at both 3-months and 12-months combining QALYs for both the young person (using the CHU9D) and the primary parent/caregiver (using the EQ-5D-5L). Appropriate sensitivity analyses will be carried out, dependent on any assumptions made in relation to the costing of the intervention, the method of measurement of outcomes or the approach to combining QALYs for young people and their primary carer.

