#### OPTIMA Assessment & Diagnosis Form

#### 1. Has the child been formally assessed by the services they were referred to?

Yes (go to question 2)

No (end of form)

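### The 12-month relative risk for ADHD diagnosis is a valid total effect, but it mixes any STEPS effect on being assessed with any effect on diagnosis once assessed, and the stated analysis does not separate the two

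*Protocol*

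**What the plan says.** The objective appears in the Synopsis (section 1) and in section 5.3: an "exploratory analysis to see if STEPS reduces the likelihood of a clinical diagnosis being made and medication prescribed by the 12 months follow up".

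- **Diagnosis (section 10.3.5).** "A presence of ADHD diagnosis will be coded as 1 and absence as 0". The source is the medical record at 12 months, or the parent if the record cannot be reached.
- **Medication (section 10.3.6).** Any drug treatment for a neurodevelopmental or mental health disorder counts, from the same sources. Assessment is not a precondition.
- **Analysis (section 19.1).** Modified Poisson regression with robust standard errors gives STEPS vs WAU relative risks "for getting a diagnosis and being prescribed medication".
- **Form (Appendix 1).** Question 1 asks: "Has the child been formally assessed by the services they were referred to". The answer No ends the form, before the diagnosis question (3) and the treatment and medication questions (6 and 7). For assessed children, question 2 records the date.

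Neither the outcome list in section 1 nor section 19.1 uses assessment status or date.

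**The concern.** Every child enters the trial while waiting for assessment, and the referred service can diagnose only after it has assessed. A lower relative risk could therefore mean that fewer assessed children were diagnosed, or that fewer children had been assessed by 12 months. These carry different messages for a service deciding whether to offer the app.

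The protocol gives some reason to expect that assessment uptake could differ by arm, in either direction. Section 4 says that long waits may lead to "a decrease in motivation, poorer engagement and premature dropout with regard to future treatment" and that the app tells parents how to reach the clinical service. Section 11 plans to ask clinicians how far the app prepares families for the formal assessment.

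Unassessed children at 12 months are also plausible. Section 8.1 admits children after anything up to nine months on the list, and section 9.4 expects no assessments in the first three months after randomisation.

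At stake is how one exploratory result is reported: a difference in assessment could be published as a reduction, or an increase, in diagnosis.

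**Working it through.** **1. The plan's own figure.** Section 13 uses d = 0.4, "a two-sided test and an alpha of 0.05", 90% power, zero baseline correlation and 25% drop-out.

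- n per arm = 2 × (1.960 + 1.282)² / 0.4² = 2 × 10.51 / 0.16 ≈ 131.4, so 132.
- 132 / (1 − 0.25) = 176.

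This reproduces "176 individuals will be needed per trial arm (total n = 352) to provide 90% power". The protocol gives no figure for diagnosis or medication.

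**2. Decomposition.** For diagnoses by the referred service, within each arm:

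P(diagnosed by 12 months) = P(assessed by 12 months) × P(diagnosed | assessed)

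so the planned relative risk = (ratio of assessed proportions) × (ratio of diagnosis once assessed).

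**3. Illustration.** All rates here are assumptions. Take P(diagnosed | assessed) = 0.70 in both arms, so the second ratio is exactly 1, and 176 per arm. SE(log RR) = √[(1 − p₀)/(176 p₀) + (1 − p₁)/(176 p₁)].

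| Assessed, WAU | Assessed, STEPS | Diagnosed, WAU (p₀) | Diagnosed, STEPS (p₁) | RR | 95% CI |
|---|---|---|---|---|---|
| 60% | 60% | 0.42 | 0.42 | 1.00 | not needed |
| 60% | 50% | 0.42 | 0.35 | 0.83 | 0.64 to 1.09 |
| 60% | 40% | 0.42 | 0.28 | 0.67 | 0.50 to 0.89 |
| 60% | 70% | 0.42 | 0.49 | 1.17 | 0.93 to 1.47 |

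Second row in full: SE = √(0.58/73.92 + 0.65/61.6) = 0.136; log 0.833 = −0.182; −0.182 ± 1.96 × 0.136 gives 0.64 to 1.09.

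On these rates, 60% vs 50% would be nominally significant in 21% of trials with 132 per arm and 27% with 176. For 60% vs 40% the figures are 67% and 79%.

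**4. Masking.** The mixture can also hide an effect. Suppose the ratio once assessed is truly 0.80 (0.70 on WAU, 0.56 on STEPS), and assessment is 50% on WAU and 62.5% on STEPS. Then 0.50 × 0.70 = 0.35 and 0.625 × 0.56 = 0.35, so the relative risk is 1.00.

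**5. How many children might be unassessed at 12 months.** The protocol does not say. As a rough range, assume entry spread evenly over 0 to 9 months on the list and one common total wait of W months. The unassessed share is (W − 12)/9 for W between 12 and 21 months, and zero for W of 12 or less.

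- W = 12: 0%
- W = 15: 3/9 = 33%
- W = 18: 6/9 = 67%

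The delay of up to 200 days in section 4 (about 6.6 months) falls in the zero range. Sections 8.1 and 9.4 together imply at least 9 + 3 = 12 months for children who enter at the nine-month limit. The waits of 15 and 18 months are assumptions, not protocol figures.

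**6. Medication.** Under section 10.3.6 an unassessed child with a prescription counts as 1. Under Appendix 1 the form has stopped before that child's prescription can be entered. The two do not agree.

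**The case against.** The strongest reply is that the objective asks about diagnosis and prescription by 12 months. A child not assessed by then has, truthfully, not been diagnosed by that service. Comparing all randomised children on that basis gives a valid total effect, whatever the pathway. This stands: the estimate is not biased for its stated target, and a reader who inferred that a relative risk below 1 would be a false finding would go too far.

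Three further inferences are tempting and unsupported.

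- *That the two effects cannot be told apart.* Appendix 1 collects assessment status for every child and the date for those assessed. The stated analysis simply does not use them.
- *That the protocol scores unassessed children as 0 on both outcomes.* For diagnosis this is inferred from the presence/absence rule and the form routing; no sentence sets the code. For medication, section 10.3.6 points the other way.
- *That many children will be unassessed.* The share may be nil. Section 19.3 describes the 12-month economic analysis as one "to assess cost-effectiveness subsequent to formal assessment and treatment", which suggests that the authors expect most assessments to have happened by then.

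The mechanism is also thin. Both arms wait, the access information is a Frequently Asked Questions entry, and the clinician interviews explore perceptions. The arm differences of 10 to 20 points are assumed, and both 10-point examples have intervals that include 1.

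Finally, section 19.2 leaves further analysis detail to a statistical analysis plan, and a companion model or table could sit there. That is fair as to where the detail goes. It does not answer the point that the protocol fixes an objective about the likelihood of diagnosis and a single contrast for it, without saying what that contrast can show.

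**Conclusion.** The point holds as one of interpretation. The planned relative risk for ADHD diagnosis is a valid total effect by 12 months. For diagnoses by the referred service it cannot, as analysed, be read as an effect on the diagnostic decision, because any effect on whether or when a child is assessed is folded in.

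The size depends on two quantities the protocol does not give: the share assessed by 12 months, and any difference in that share between arms. With equal diagnosis once assessed, a 10-point shortfall from 60% moves the relative risk to 0.83 and a 20-point shortfall to 0.67. With everyone assessed, or equal shares in both arms, there is no distortion.

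The medication outcome as defined in section 10.3.6 is not limited to assessed children. Its problem is the conflict with the form routing. Only an exploratory objective is affected; the primary analysis and the 352 participants are not.

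**What to change.** - Keep the all-randomised relative risks. In objective 5, describe them as total effects on diagnosis, or on medication, by 12 months, and not as effects on the diagnostic decision.
- State how a child not assessed by 12 months is coded for diagnosis.
- Add formal assessment by 12 months (Appendix 1, questions 1 and 2) as a companion exploratory outcome in the same modified Poisson model.
- Tabulate by arm: not assessed; assessed without diagnosis; assessed with diagnosis.
- Adjust these models for time on the waiting list at randomisation, taken from the records used for the eligibility check in section 8.1. The Appendix 1 form does not hold this item.
- Do not restrict the comparison to assessed children, and do not make the conclusion depend on whether the assessed proportions appear to explain a difference. The first conditions on a post-randomisation event; the second is an undefined mediation rule on one.
- For medication, count any prescription found in the records or reported by the parent, as section 10.3.6 states, whatever the assessment status. Reconcile that section with the Appendix 1 routing so that unassessed children are not lost.

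The cost is one extra model, one table, one item kept from screening, a correction to the form routing, and more cautious wording of an exploratory result.

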## 2. Revision History

| Document ID - (Document Title) revision X.Y | Description of changes from previous revision                                                                                                                                                                                                                                                    | Effective Date |
|----------------------------------------------------|---------------------------------------------------------------------------------------------------------------------------------------------------------------------------------------------------------------------------------------------------------------------------------------------------------|-----------------------|
| V.2.1 15 November 2021                             | 
 
1. Push notifications sent from the STEPS app will be replaced with text messages also sent from the app (p. 19).
 
2. Telephone interviews will be recorded via Microsoft Teams and not audio capture software installed on a laptop (p. 32).
 
 |                       |

|                     |                                                                                                                                                                                                                                                                                                                                                                                                                                                                                                                                                                                                                                                                                                                                                                                                                                                                                                                                                                                                                                                                                                                                                                                                                                                                                                                                                                                                                                                                                                      |  |
|---------------------|------------------------------------------------------------------------------------------------------------------------------------------------------------------------------------------------------------------------------------------------------------------------------------------------------------------------------------------------------------------------------------------------------------------------------------------------------------------------------------------------------------------------------------------------------------------------------------------------------------------------------------------------------------------------------------------------------------------------------------------------------------------------------------------------------------------------------------------------------------------------------------------------------------------------------------------------------------------------------------------------------------------------------------------------------------------------------------------------------------------------------------------------------------------------------------------------------------------------------------------------------------------------------------------------------------------------------------------------------------------------------------------------------------------------------------------------------------------------------------------------------|--|
| V.2.2. 01 July 2022 | 
 
1. Change to the character of an outcome: Mean rating of child oppositional and defiant speech during an online parent-child drawing task, Etch-a-Sketch Online, measured with independent observer ratings on Childhood Oppositional and Defiance Speech Sample Scale has been changed from secondary to exploratory outcome. A clear distinction has also been made between the secondary and exploratory outcomes.
 
2. Addition of a new exploratory outcome: Mean parent-rated child emotional problems measured with the respective subscale of the Strengths and Difficulties Questionnaire.
 
3. Changes to the study team: 
 
- [name] has replaced [name] as the OPTIMA PPI Panel Chair.
 
- [name] has replaced [name] as the Trial Statistician.
 
- [name] stepped down from her role as the interim co-lead for the Nottingham Trial Centre.
 
 
 
4. Correction of a typographical omission on p. 23. 10.3.8 Experience of parenting – T1 in now included in the subheading.
 
5. Changes to the amount of information collected by the STEPS app (p. 44). Following a recent update, STEPS no longer collects information about IP addresses and device IDs.
 
6. Addition of a definition of the study end date (p. 16).
 
 |  |
|---------------------|------------------------------------------------------------------------------------------------------------------------------------------------------------------------------------------------------------------------------------------------------------------------------------------------------------------------------------------------------------------------------------------------------------------------------------------------------------------------------------------------------------------------------------------------------------------------------------------------------------------------------------------------------------------------------------------------------------------------------------------------------------------------------------------------------------------------------------------------------------------------------------------------------------------------------------------------------------------------------------------------------------------------------------------------------------------------------------------------------------------------------------------------------------------------------------------------------------------------------------------------------------------------------------------------------------------------------------------------------------------------------------------------------------------------------------------------------------------------------------------------------|--|

